## Abstract

**Background:**

There are an estimated three million people in the United Kingdom with chronic obstructive pulmonary disease (COPD), and the incidence of bronchiectasis is estimated at around 0.1% but is more common in COPD and severe asthma. Both COPD and bronchiectasis are characterized by exacerbations in which bacteria play a central role. Pseudomonas aeruginosa is isolated from sputum samples from 4% to 15% of adults with COPD and is more likely to be isolated from patients with severe disease. Earlier detection of exacerbations may improve morbidity and mortality by expediting treatment. Aseptika Ltd has developed a system for patients to self-monitor important physiological measurements including levels of physical activity, peak flow, forced expiratory volume (FEV1), and biomarkers for P aeruginosa in sputum.

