### Sampling and Sample Size

Using the sputum biomarkers to predict exacerbations, we based the sample size on the difference in exacerbation frequency in time periods when an exacerbation was predicted compared to time periods when no exacerbation was predicted. This will give an odds ratio of exacerbation following detection of sputum biomarkers.

Time periods will consist of approximately 10 days, of which it will be estimated that there may be on average 12 per participant (assuming an average of 4 months of follow-up). It is estimated that an exacerbation will occur in 60% of time periods in which it is predicted and 10% of time periods in which it is not predicted. It is also assumed that a predicted exacerbation will be made in only 1 in 12 time points (8% of all time points). Using a 5% significance level and 90% power, it is calculated a total of 120 time periods will be required.

However, as there are multiple time periods from the same participant, the data values are unlikely to be independent of each other and thus the sample size requires inflating. Assuming intraclass correlation of 0.18, a design effect of approximately 3 is calculated. This implies that 360 time periods are required for the analysis. This equates to a total of 30 participants for the study. The proposed 30 participants will consist of 20 participants with chronic *P aeruginosa* infection (10 with primarily COPD and 10 with NCFB) and 10 participants with *H influenzae* infection.

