#### Analysis of Endpoints

The first stage of the data analysis is to use data on the collected parameters (eg, peak flow, pulse rate, oxygen saturation, activity data) to predict when an exacerbation is likely. Control charts will be used to determine the boundaries of normal behavior for each parameter. Separate control charts will be used for each participant, as what constitutes normal behavior will vary from participant to participant. When a parameter strays from normal behavior (eg, exceeds 99% control limits), an exacerbation will be predicted.

To examine the association between predicted exacerbation and actual exacerbation, participant follow-up will be divided into periods of time (eg, 7-10 days). A comparison of actual exacerbation when exacerbation has and has not been predicted will be made. To allow for the repeat measurements over time from the same participants, the analysis will be performed using multilevel logistic regression. Additionally, the sensitivity and positive predictive value of the predictions will also be calculated. Estimated values will be presented along with corresponding confidence intervals. Further exploratory analysis using novel computing methods will be conducted.

Health care use data will be presented descriptively (eg, the frequency and type of health care contacts over the study period for different participant groups).

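### The primary comparison scores alarm and exacerbation by block of about 7-10 days with no rule that the alarm comes first, so it favours coincident signals over early ones

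*Protocol article*

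**What the plan says.** Analysis of Endpoints raises a prediction when a parameter leaves the participant's own control limits (99% limits are the example). It then says that "participant follow-up will be divided into periods of time (eg, 7-10 days", and that "A comparison of actual exacerbation when exacerbation has and has not been predicted will be made". Multilevel logistic regression is the model; sensitivity and positive predictive value (PPV) are also to be reported.

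Sampling and Sample Size shows the unit on which both are scored. It says "Time periods will consist of approximately 10 days", with this assumption: "an exacerbation will occur in 60% of time periods in which it is predicted and 10% of time periods in which it is not predicted". The same section states the quantity sought: "This will give an odds ratio of exacerbation following detection of sputum biomarkers".

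The Primary Endpoint section dates an exacerbation by the start of, or change in, antimicrobial therapy. Participant and Carer Training asks participants to go on recording if they are admitted, so readings continue after onset. The Primary Objective is prediction, and the Abstract's motive is that "Earlier detection of exacerbations may improve morbidity and mortality by expediting treatment".

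Nowhere does the article require the alarm to precede the antibiotic start, set a lead window, stop counting alarms at onset, or deal with an alarm in one block and an onset in the next.

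**The concern.** A table of blocks classified by alarm (yes or no) and exacerbation (yes or no) cannot tell before from after. The event is dated by the start of treatment, when the participant already has symptoms. Lung function, saturation, temperature or activity may well leave their limits on that day or just after it, and each such alarm would be credited as a prediction. A warning several days ahead can instead fall on the far side of a block boundary and lose its credit.

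The Discussion says that the data will be used to determine the key elements of the monitoring system and so reduce the monitoring burden. If the accuracy measures rank a marker with no lead time above one that warns early, the wrong elements may be kept. The planned comparison would then not deliver the target that the sample-size section sets for it.

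**Working it through.** **1. The plan's own figures.** Inputs from Sampling and Sample Size: 60% against 10%; "a predicted exacerbation will be made in only 1 in 12 time points (8% of all time points"; "on average 12 per participant (assuming an average of 4 months of follow-up"; 5% significance, 90% power, intraclass correlation 0.18.
- Two-sided test of two proportions, ratio 1:11, with continuity correction: 9.4, rounded up to 10 predicted periods; 10 × 12 = 120.
- Design effect: 1 + (12 − 1) × 0.18 = 2.98, about 3. Then 120 × 3 = 360 periods, and 360 / 12 = 30 participants.

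The stated figures reproduce and are not in dispute.

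**2. The table this implies for 360 periods.** Predicted: 360 / 12 = 30, giving 18 true and 12 false positives. Not predicted: 330, giving 33 misses and 297 true negatives. PPV = 18/30 = 60%; sensitivity = 18/51 = 35%; odds ratio (OR) = (18 × 297)/(12 × 33) = 13.5; event rate = 51/360 = 14.2% of periods.

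**3. Chance that a boundary separates alarm from onset.** With onset uniform within a block of W days, an alarm L days ahead lies in an earlier block with probability min(1, L/W).

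| L (days) | W = 10 | W = 7 |
|---|---|---|
| 1 | 10% | 14% |
| 3 | 30% | 43% |
| 5 | 50% | 71% |
| 7 | 70% | 100% |

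**4. Effect on the planned table.** Suppose all 18 true positives are isolated early alarms and a share c crosses a boundary into a block that would otherwise be a true negative. The cells become 18(1 − c), 12 + 18c, 33 + 18c and 297 − 18c.

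| c | PPV | Sensitivity | OR |
|---|---|---|---|
| 0 | 60% | 35% | 13.5 |
| 0.1 | 54% | 32% | 10.0 |
| 0.3 | 42% | 25% | 5.5 |
| 0.5 | 30% | 18% | 2.9 |

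For c = 0.3: (12.6 × 291.6)/(17.4 × 38.4) = 5.5.

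**5. Simulation of different alarm shapes.** The event rate comes from the plan: (1/12)(0.6) + (11/12)(0.1) = 14.2% per 10 days. Assumed: 180 days per participant, events more than 14 days apart (which lowers the realised rate slightly), 60% of exacerbations detected, 4% background alarms per block, 10-day blocks.

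| Alarm pattern | Same-block sensitivity | Same-block PPV | Same-block OR | Onsets with an alarm in the 10 days before |
|---|---|---|---|---|
| Start day only | 62% | 69% | about 38 | 4% |
| One alarm, 5 days ahead | 33% | 37% | about 6 | about 61% |
| Day -5 to day 0 | 62% | 53% | about 19 | about 61% |

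The marker with almost no warning value scores highest. The sustained early alarm keeps its sensitivity and loses only through extra false-positive blocks.

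**6. Sensitivity to the assumptions.** At 35% detection, close to the sensitivity in step 2, the start-day marker gives OR about 15 and the day -5 to 0 alarm about 9. If the background follows nominal 99% limits at 1% per day, it is 1 − 0.99^10 = 9.6% per block; at 60% detection the two ORs are then about 17 and 11. With 7-day blocks and the settings of step 5, the single alarm five days ahead falls to about 3, against more than 50 for the start-day marker. The ranking is the same in every setting tried.

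**The case against.** Four objections carry weight.

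- **The same-block rule is inferred.** A reader might take the protocol to state that alarms after the antibiotic start count as correct. It does not. Analysis of Endpoints does not say that alarm and event are matched within one block; that reading comes from the sample-size wording, which could also mean the period for which an exacerbation is forecast. The only text on order points towards prediction. What stands is that this intended order is not carried into the scoring.
- **An analysis plan may settle it.** The article refers to a statistical analysis plan that is not shown, and block lengths are given only as examples. Lead windows could be set there. However, the comparison that the article does describe, read as above, fails to meet the article's own target, so the point is more than an omitted detail.
- **The double penalty is not general.** A reader might infer that every boundary-crossing warning is both a false alarm and a miss. That needs an alarm confined to the earlier block, no exacerbation in that block, and silence in the onset block. Monitoring is daily, and a deteriorating parameter may stay outside its limits until onset; the miss then disappears. The contrast of 38 against 6 is the least favourable case.
- **The stakes are limited.** This is a 30-person development cohort whose data guide no care, and effectiveness is left to a later randomised trial. That argues against treating the point as critical. It does not remove the bias in choosing which markers to keep.

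**Conclusion.** The point holds in this form: the described comparison has no time order, although the protocol wants exacerbation following detection. On the natural reading of the two sections, the odds ratio, sensitivity and PPV favour signals that coincide with or follow treatment over signals with lead time. The direction persists across the detection rates, background rates and block lengths examined.

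The size is not fixed by the documents, because they give no alarm timing. Under the assumptions shown, the start-day marker's odds ratio exceeds that of an early marker by a factor of about 1.5 (17 against 11, sustained alarm with higher background) to about 6 (38 against 6, isolated alarm five days ahead) with 10-day blocks. The sample-size arithmetic is unaffected. The point should be fixed, but it does not invalidate the study.

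**What to change.** Add to Analysis of Endpoints:
- Alarm status is set only from readings before the antibiotic start, while the participant is exacerbation-free.
- The outcome is an antibiotic start within a prespecified window after the alarm assessment, for example the next 7-10 days.
- Alarms dated on or after the start day do not count as predictions.
- The odds ratio, sensitivity and PPV are computed on this basis with participant-level clustering, and the distribution of lead times is reported.

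Daily assessment with overlapping windows and assessment at the start of each block are both acceptable; the choice should be stated before the analysis.

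Cost: wording and some extra programming, since readings are daily and antibiotic starts are recorded. Overlapping windows need clustered intervals. Reported accuracy will probably be lower than under same-block scoring.

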### Primary and Secondary Endpoints and Outcome Measures

#### Primary Endpoint

An exacerbation will be defined as the initiation of antimicrobial therapy for respiratory symptoms either at home or on admission, with or without concomitant steroids or admission. For participants who are already on continuous antibiotics, an exacerbation will be defined as starting a course of different antibiotics or increasing the dose or frequency of existing antibiotics due to increased symptoms.

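### The primary comparison scores alarms and exacerbations by 7-10 day period without requiring the alarm to come before antibiotics start, so it cannot separate prediction from concurrent detection

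*Protocol article*

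**What the plan says.** All references are to the protocol article.

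- **Alarm rule (Analysis of Endpoints).** "When a parameter strays from normal behavior (eg, exceeds 99% control limits), an exacerbation will be predicted". No days are excluded.
- **Unit (same section).** "participant follow-up will be divided into periods of time (eg, 7-10 days").
- **Comparison (same section).** "A comparison of actual exacerbation when exacerbation has and has not been predicted will be made", by multilevel logistic regression, with sensitivity and PPV in addition.
- **Sampling and Sample Size.** The unit is again the period, and the planning assumption reads: "an exacerbation will occur in 60% of time periods in which it is predicted and 10% of time periods in which it is not predicted". The stated target is directional: "This will give an odds ratio of exacerbation following detection of sputum biomarkers".
- **Primary Endpoint.** "An exacerbation will be defined as the initiation of antimicrobial therapy for respiratory symptoms either at home or on admission".
- **Recording.** Study Assessments asks for daily measurements over 6 months. Participant and Carer Training asks participants to keep recording if they are admitted.
- **Aim.** The Primary Objective is to build models that predict an exacerbation, and the abstract speaks of exacerbations that are still to come.

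**The concern.** The aim has a time order: first a signal, then an exacerbation. The comparison as described has none. The event date is the day antibiotics start, when symptoms are already present, and readings continue daily through treatment. Abnormal values on that day and just after it are to be expected. If they fall in the same period as the onset, that period is scored as a correct prediction, although the reading gave no warning.

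At stake is what a positive primary result would mean. A marker that only reflects current illness could reach the planned effect, and the result would not show that exacerbations can be predicted.

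The grid also errs in the other direction. A true alarm late in one period, followed by onset early in the next, is scored as one false positive and one false negative.

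**Working it through.** **1. The plan's own figures.** Inputs from Sampling and Sample Size: 60% and 10% event rates, alarms in 1 of 12 periods, 5% significance, 90% power, 12 periods per participant, intraclass correlation 0.18.

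- Two proportions, two-sided (sidedness is not stated), continuity-corrected, allocation 1:11: 10 + 110 = 120 periods, as stated.
- Design effect: 1 + (12 − 1) × 0.18 = 2.98. 120 × 2.98 = 357.6, stated as 360. 360 / 12 = 30 participants.
- Planned odds ratio: (0.6/0.4) / (0.1/0.9) = 13.5.
- Periods with an exacerbation: 0.6 × 1/12 + 0.1 × 11/12 = 0.1417, or 12 × 0.1417 = 1.7 per participant.
- Implied sensitivity: 0.05 / 0.1417 = 35%.

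The arithmetic reproduces. It has no timing input, so it neither causes nor reveals the problem.

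**2. A marker with no lead time, at the study's size.** 1,000 simulated studies per scenario, 30 participants × 12 ten-day periods, 14.17% of periods with an onset. Assumed, not in the document: the marker is abnormal only from antibiotic start, for 7 days. The odds ratio comes from the pooled two-by-two table. Significance uses the log odds ratio variance multiplied by 2.98, as a stand-in for the multilevel model.

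| Background alarm per day | Post-onset alarm per day | Same-period median OR | Sensitivity | PPV | Significant |
|---|---|---|---|---|---|
| 0.005 | 0.10 | 9.5 | 43% | 50% | 99.7% |
| 0.005 | 0.20 | 19.3 | 65% | 55% | 100% |
| 0.005 | 0.30 | 33.3 | 79% | 57% | 100% |
| 0.01 | 0.10 | 6.4 | 46% | 39% | 97.9% |
| 0.01 | 0.20 | 13.6 | 67% | 46% | 100% |
| 0.01 | 0.30 | 23.4 | 80% | 48% | 100% |

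One scenario with 7-day periods (0.005 and 0.20) gave 14.7.

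With order imposed (alarm in the preceding period, alarms ignored from antibiotic start to day 14), the same markers gave a median OR of 1.05 to 1.16, significant in 0 to 0.2% of studies. A pure-noise marker in the same program gave 1.11 under same-period scoring, so 1.05 to 1.16 amounts to no association.

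**3. The same question in a large sample.** 3,000 participants × 180 days, background alarm 1/12 per 10 days, 7 abnormal days after onset, 14-day episodes (the last two assumed). Same-period OR was 3.3, 6.1 and 21 at daily post-onset alarm probabilities of 5%, 10% and 28%. At 28%, sensitivity was 76% and PPV 45%. The 28% corresponds to a 2-SD shift against 99% limits: P(Z > 2.576 − 2) ≈ 0.28. Forward, off-treatment scoring of the same data gave 0.93 to 1.00.

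**4. The grid error.** With onset uniform within the period, a true lead of d days falls in the preceding period with probability d divided by the period length. For 3 days this is 3/10 = 30%, or 3/7 = 43% with 7-day periods. For 5 days in 10-day periods it is 50%.

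**The case against.** The document never says in so many words that alarm and event are compared within the same period. Where it speaks to order, it points forward, as in "This will give an odds ratio of exacerbation following detection of sputum biomarkers". The period length and control limits are marked as examples. The article condenses a fuller plan, and lead windows and at-risk rules often sit in an analysis plan, which is not shown here.

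Part of this stands. Same-period scoring is the natural joint reading of the two sections, not a stated rule, and an unseen plan may add a lead rule. But the article does more than leave a detail out: it fixes the alarm rule, the unit, the comparison, the model and the accuracy measures. Followed as written, these do not carry out the intended order.

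Three stronger readings are tempting and not supported:

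- **That periods during treatment and recovery certainly stay in the analysis.** The document does not exclude them, but it does not say they are kept. The analysis population section includes all subjects, which is not the same as all days.
- **That a home course followed by a course on admission counts as two exacerbations.** The Primary Endpoint wording describes where one event may start, and Secondary Endpoints speaks of treatment for an episode. A change of antibiotics is named as an event only for participants already on continuous antibiotics.
- **That the study will produce a spurious result.** The simulations show what the described scoring permits under assumed alarm rates, not what these data will show.

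**Conclusion.** The point holds in this form: the comparison as described does not require the alarm to precede the start of antibiotics, so its odds ratio, sensitivity and PPV cannot tell prediction from concurrent detection. That conflicts with the Primary Objective and with the sample size section's own directional target.

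The size depends on post-onset alarm rates, the 7-day abnormal window and 14-day episodes, none of which are in the document. Over daily alarm probabilities of 5% to 28%, a marker with no lead time gives a same-period odds ratio of about 3 to 21, against the planned 13.5, and about 1 when scored forward. The direction was the same in every scenario tried. The study-size significance rates use a design-effect stand-in and not the multilevel model itself. The sample size arithmetic is unaffected.

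**What to change.** Score forward in time.

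- **At risk.** Assess on days t when the participant is not within an open treated episode.
- **Alarm.** Use only at-risk data up to day t, with the look-back stated in advance. Readings from antibiotic start to the end of that episode do not count as alarms.
- **Outcome.** The first antibiotic start of a new episode in days t+1 to t+10, matching the 10-day period used for the sample size.
- **Model.** Keep the multilevel logistic regression, with a participant-level bootstrap if windows overlap. Report the lead time of correct alarms beside sensitivity and PPV.
- **Assumptions.** Restate the 60% and 10% for this definition.

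Do not take the shortcut of relating the alarm in one period to onset in the next while dropping periods that overlap treatment. Onset is the start of treatment, so taken literally that rule deletes every event. It would also miss a true 3-day lead 70% of the time (1 − 3/10). The lagged comparison in the working serves only to show that imposing order removes the artefact.

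**Cost.** Analysis wording and programming only. Sample containers carry the date and antimicrobial starts are entered in the system (Data Management). The Results section says the study is in data analysis, so the change should be recorded under the article's own provision for documented deviations.

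The downside is a smaller denominator. With 14-day episodes (assumed), an onset uniform within a 10-day period overlaps 1.3 later periods on average (one for 7 of the 10 possible onset days, two for the other 3). Then 1.7 × 1.3 = 2.2 of 12 periods, or 18%, are lost, or about 17% allowing for overlap between episodes. That leaves roughly 295 to 300 of the planned 360.

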#### Procedure for Dealing with Missing, Unused, and Spurious Data

The primary analysis will be restricted to collected data only, without any data imputation. The distributions of the parameters collected will be assessed, and implausible values may be excluded from the analysis. Any data exclusions will be justified both clinically and statistically.

#### Procedures for Reporting any Deviations From the Original Statistical Analysis

Any deviations to the statistical analysis plan will be carefully documented and justified.

### Ethics

#### Overview

The study will not be initiated before the protocol and all study-relevant material such as informed consent forms and participant and general practitioner information sheets have received approval or favorable opinion from the Research Ethics Committee (REC) and the respective NHS research and development department. Any changes to protocol or relevant study documents will be approved by the sponsor. Should an amendment be made that requires REC approval, defined by REC as a substantial amendment, the changes will not be instituted until the amendment has been reviewed and received approval or favorable opinion from the REC and research and development departments. A protocol amendment intended to eliminate an apparent immediate hazard to participants may be implemented immediately providing that the REC is notified as soon as possible and an approval is requested. Minor amendments, defined by REC as nonsubstantial amendments, may be implemented immediately and the REC will be informed.

